### Data management

The study steering committee is comprised of two PhD students (blind evaluators), two master’s students (responsible for data collection), two undergraduate students (responsible for data tabulation and codification), a coordinator (responsible for managing the project) and an assistant Research (responsible for the recruitment and scheduling of collections).

All information collected during the protocol will be entered onto an electronic form by those responsible for data collection. The integrity and validity of the data will be verified at the time of data entry (edit checks). Identification of potential recruits will be done by the project manager and the research assistant. The research assistant will be trained on how to approach the eligible participants during the initial recruitment contact for the survey (made by telephone calls) and how and when to contact them for follow-up and data collection.

### Oversight and monitoring

The Data Monitoring Committee (Steering Committee) and the Faculdade de Medicina da Universidade de Sao Paulo Board will regularly monitor (depending on the recruitment numbers and collections performed) the study datasets and make recommendations on necessary protocol modifications or termination of all or part of the study. A trimester meeting is held to facilitate the study development. All team members can request meetings as needed.

All adverse events occurring during the clinical trial period will be recorded. Minor adverse effects potentially expected are muscle soreness and tiredness after performing the proposed exercises. The patients will be advised to report any discomfort and foot preulcerative signs (blisters, callus, or even foot ulcers) to Researcher 3 who will ask for the blinded podiatrist nurse to assist the patient.

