### Randomization, allocation, and blinding

pt?>The randomization schedule has been prepared using Clinstat software [44] by an independent researcher (Researcher 1) who is not aware of the numeric coding for the control group and intervention group. A numeric block randomization sequence is kept in opaque envelopes.

Potential participants will be assessed through an initial screening that consists of checking the eligibility criteria, classifying the DPN severity, and identifying those with a lower probability of adherence to the intervention due to depression. After the initial screening, participants who meet the inclusion criteria will be randomized to either the intervention group or control group. After the agreement to participate and assignment in the research, the allocation of the groups will be made by another independent researcher (Researcher 2) who is also unaware of the codes. All participant personal data will be kept confidential before, during, and after the study by encoding the participants’ names. Only the physiotherapist (Researcher 3), who is the main researcher responsible for the intervention, is aware of who is receiving the intervention. Researcher 3 is also responsible for the remote monitoring of the intervention by the SOPeD software and by telephone. One physiotherapist and an occupational therapist (Researchers 4 and 5), who are also blind to the treatment allocation, will be responsible for all clinical, functional and biomechanical assessments. Researchers 3, 4, and 5 are blind to the block size used in the randomization procedure. The trial statistician will also be blind to treatment allocation until the main treatment analysis has been completed. The trial design is open label where only the outcome assessors are blinded so unblinding will not occur.

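### The blind evaluators sit on the committee that monitors the accumulating datasets, which leaves assessor blinding less protected than the protocol claims (minor)

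*Protocol article*

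**What the plan says.** Three sections of the protocol article bear on this.

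- **Oversight and monitoring** treats the monitoring committee and the steering committee as one body, working alongside the faculty board: "The Data Monitoring Committee (Steering Committee) and the Faculdade de Medicina da Universidade de Sao Paulo Board will regularly monitor". Its remit covers "the study datasets and make recommendations on necessary protocol modifications or termination of all or part of the study". How often it reviews depends on recruitment and on the data collected so far. A separate sentence provides for a meeting each trimester to help the study along. The same section has all adverse events recorded.
- **Data management** gives the membership: "The study steering committee is comprised of two PhD students (blind evaluators), two master’s students (responsible for data collection"). The other members are two undergraduates who tabulate and code the data, a coordinator and a research assistant who handles recruitment and scheduling.
- **Randomization, allocation, and blinding** describes two assessors "who are also blind to the treatment allocation, will be responsible for all clinical, functional and biomechanical assessments". On knowledge of allocation it says: "Only the physiotherapist (Researcher 3), who is the main researcher responsible for the intervention, is aware of who is receiving the intervention". It then states: "The trial design is open label where only the outcome assessors are blinded so unblinding will not occur". The statistician is covered separately: "The trial statistician will also be blind to treatment allocation until the main treatment analysis has been completed".

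**The concern.** Participants know their arm, and so does the physiotherapist who runs the intervention. What protects the measured outcomes from expectation bias is that the assessors do not know. The article nevertheless gives those assessors a second role, as members of the body that reviews accumulating data and may advise changing or ending the trial. Doing that job properly means looking at safety, retention and adherence, which is the information most likely to identify who is exercising.

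An assessor who learns or guesses the arm of a participant carries that knowledge into the 12-week and 24-week assessments. Any resulting error would probably run in one direction, and neither the intention-to-treat nor the per-protocol analysis would remove it.

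**Working it through.** There is no figure in the plan to reproduce and no arithmetic to do. The check is to set the sections side by side.

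**1. Are the evaluators on the monitoring body?** Oversight and monitoring identifies the Data Monitoring Committee with the Steering Committee. Data management lists the steering committee's members and starts with the two blind evaluators. The overlap is stated outright. One link is inferred: that these two are Researchers 4 and 5, the blinded assessors in the randomization section. Both descriptions are of two blinded people who do the evaluating, and no other blinded pair is named, so the inference is natural.

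**2. What would the committee look at?** The article says only that it monitors the datasets. A body that can recommend termination would be expected to see adverse events and losses from the study.

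**3. Can such records show the arm without a group label?**
- *Adverse events.* The minor events the article expects are soreness and tiredness following the exercises. Only the intervention group is assigned these exercises. A participant with such an entry goes on to later assessments, so this is the more important route.
- *Terminations.* Under Intervention, an intervention participant who does not access the software for two weeks running, without explanation, is removed from the study. The rule is written for that arm only, so the reason for removal identifies the arm. Its direct effect is smaller, because a removed participant may not be measured again.
- *Adherence.* Log-in lapses and the reminders they trigger are likewise defined for the intervention group only.

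**4. Which outcomes depend on the assessor?**

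| Outcome | Role | Dependence on the assessor |
|---|---|---|
| DPN symptoms (Michigan questionnaire) | Primary | Little: self-administered |
| Fuzzy DPN severity score | Primary | Two of its three domains are monofilament and tuning-fork findings |
| Tactile and vibration sensitivity | Secondary | Direct: for vibration, the evaluator times the interval until their own hand stops feeling the fork |
| Toe-flexor strength | Secondary | A physiotherapist decides whether a trial is discarded |
| Gait kinematics, kinetics and plantar pressure | Secondary | Less: instrumented, but valid steps must be obtained and markers placed |

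**5. Is there a stated barrier between the two roles?** The article keeps the statistician blind until the main analysis is done and has the satisfaction form opened only after the study is complete. It states no comparable barrier for evaluators acting as committee members.

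**The case against.** The strongest defence is that the article already limits who knows what. Knowledge of allocation is reserved to Researcher 3, who also does the remote monitoring. The monthly self-assessment reports go to the participant and the main researcher. Names are encoded, and the assessors do not know the block size. No section says that log-ins, exercise reports or results by group enter the datasets the committee reviews. This stands to the extent that **actual unblinding is not shown**, and a reader who concludes that the evaluators will see allocation goes beyond the text. It does not dispose of the point, because removing the group code does not mask an entry whose content belongs to one arm.

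A second defence is that the sentence on unblinding may mean only that an open-label trial needs no code-break procedure. That is a fair reading. The tension is then with the reliance placed on blinded assessors, not with the literal claim, and it remains.

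A third is that a condensed article leaves committee procedures to the full protocol or a charter. That holds for masking of reports and for stopping rules, whose absence is no finding. The overlap of roles is different, because the article itself states it.

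A reader might also infer that repeated reviews with power to recommend termination inflate the 5% error rate. The documents do not support this. No comparison by arm before the main analysis and no stopping for benefit is described, and the statistician is blind until that analysis is finished. The trimester meeting is for running the study. Counting each meeting as a significance test would assume a design that the article does not contain.

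**Conclusion.** The point holds as a conflict of roles and is minor. The article places the blind evaluators on the body that monitors the data and may recommend changes or termination, while relying on their blindness as the main safeguard of an open-label trial. The risk falls on the severity score and on the assessor-dependent secondary outcomes, not on the self-administered symptom score. It cannot be expressed as a number, because the article does not say what the committee sees.

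The conclusion rests on two assumptions: that the blind evaluators under Data management are the assessors in the randomization section, and that a committee able to recommend termination would see participant-level adverse events or reasons for leaving. If the full protocol already keeps such records from the evaluators, only the wording of the article needs attention. The planned 5% level is not called into question.

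**What to change.** Revise Data management and Oversight and monitoring together so that they state:

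1. The blind evaluators take no part in reviewing participant-level adherence, adverse-event or termination data, or any results by group.
2. They may see recruitment, data completeness and data pooled over both arms.
3. The remaining committee members and the faculty board carry out the rest of the review and make any recommendation that follows from it.

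This presumes that the remaining members do not themselves take outcome measurements. Any who do should follow the same rule.

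The cost is a short paragraph and a recusal rule. The evaluators lose a say on some agenda items. No new staff, separate committee, or change to the sample size or analysis is needed.

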### Sample size and statistical analyses

The sample calculation was performed using the GPower v.3.1 program [60]. Two outcomes of extreme functional importance for patients with DPN were used to calculate the sample size. Considering the primary outcome (DPN symptoms), a medium effect size (0.52) was adopted and, for the secondary outcome (peak pressure at forefoot), a small effect size (0.20) was adopted. Both effect sizes were taken from the study by Sartor et al. [30] which evaluated the effect of a 12-week supervised physical therapy exercise in patients with DPN. In order to obtain the largest sample size, the smallest effect size (0.20) was used. A statistical design of F-test repeated measures and interaction between and within factors with two repeated measures and two study groups, a statistical power of 0.80, an alpha of 0.05, and an effect size of 0.20 were used for the sample size calculation. The resulting sample size was 52 individuals. A final sample size of 62 patients was then chosen after estimating a drop-out rate of 20%.

The inferential statistical analysis will be based on an intention-to-treat analysis and per-protocol analysis. Mixed general linear models of analysis of variance for repeated measure will be used to detect treatment–time interactions (α = 5%), and the Newman–Keuls post hoc test will be used to obtain group effect (intervention group and control group), time effect (between T0 and T12), and group–time interaction. Effect sizes (Cohen’s *d* coefficient) will also be provided between T0 and T12 and between T12 and T24 to determine if the intervention shows any treatment effect. The difference between the means with their respective 95% confidence intervals will also be calculated. Imputation of any missing data for the analyzed variables will be conducted depending on the nature of the losses: missing completely at random, missing at random, or missing not at random. The per-protocol analysis will include only those patients who completed follow-up in the allocated intervention group. If there is evidence that the difference in the treatment depends on certain patient characteristics identified in the baseline assessment, a subgroup analysis will be performed.

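### The 52 patients correspond to a 0.80 SD difference in change, not the small effect described, so the scale of 0.20 and 0.52 must be settled and the detectable difference restated

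*Protocol article*

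**What the plan says.** All of this stands in the protocol article under Sample size and statistical analyses. Two outcomes supply effect sizes: for DPN symptoms and forefoot peak pressure, "a medium effect size (0.52) was adopted and, for the secondary outcome (peak pressure at forefoot), a small effect size (0.20) was adopted". Both are taken from one previous trial, "which evaluated the effect of a 12-week supervised physical therapy exercise in patients with DPN". The smaller value drives the design: "In order to obtain the largest sample size, the smallest effect size (0.20) was used".

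The software is GPower 3.1 and the test is described as "A statistical design of F-test repeated measures and interaction between and within factors with two repeated measures and two study groups". The other inputs are "a statistical power of 0.80, an alpha of 0.05, and an effect size of 0.20 were used for the sample size calculation". The outcome is stated plainly: "The resulting sample size was 52 individuals". This is raised to 62 for 20% drop-out.

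The paragraph names neither the scale of 0.20 and 0.52 nor the correlation between the two measurements. The only effect-size measure named in the section is Cohen's d, in the analysis paragraph, as a quantity to be reported with the results.

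**The concern.** The word attached to each number and the test it is fed into belong to different scales. By the usual benchmarks, d is small at 0.2, medium at 0.5 and large at 0.8. For f the values are 0.10, 0.25 and 0.40. Calling 0.20 small and 0.52 medium is right for d and wrong for f, yet the named F-test takes f.

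In a 2 × 2 interaction, one unit of f is worth four SD of between-group difference in change, so the confusion is not cosmetic. The paragraph presents the choice of 0.20 as the cautious one that gives the largest sample. A reader will conclude that the trial can detect a small effect on forefoot pressure, and so has ample power for a medium effect on the primary outcome. If the source values are d, neither conclusion follows.

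**Working it through.** **Inputs from the article:** f = 0.20 (as entered), 2 groups, m = 2 measurements, alpha 0.05, power 0.80, 1:1 allocation (Trial design). **Assumed:** correlation rho = 0.5, the software default, and the default effect-size option.

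**1. Reproduce 52.** For the within-between interaction, lambda = f² × N × m / (1 − rho), with df = 1 and N − 2.
- N = 52: lambda = 0.04 × 52 × 2 / 0.5 = 8.32; power 0.807.
- N = 50: power 0.791, below 0.80. So the minimum is 52, as stated.

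Other inputs tried with f = 0.20 do not return 52:
- rho = 0, 0.3, 0.4, 0.6 and 0.7 give 102, 72, 62, 42 and 32.
- Three measurements give 42.
- The two alternative effect-size options in the software give 202 and 200.

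**2. Translate f into a difference in change.** A between-group difference in change of delta spreads over the four cells as ± delta/4. Hence f = delta / (4 × SD) and delta = 4 × 0.20 × SD = 0.80 SD. With rho = 0.5, the SD of change is SD × √(2 × 0.5) = SD.

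Cross-check: for a two-sample t-test on change with 26 per arm and d = 0.80, the noncentrality is 0.80 × √13 = 2.884. Its square is 8.32, and power is again 0.807.

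**3. If 0.20 and 0.52 are d for a between-group difference in change** (N = 52, rho = 0.5):
- 0.52 SD: f = 0.52/4 = 0.13; lambda = 0.0169 × 208 = 3.52; power 0.452. Total N for 80%: 120.
- 0.20 SD: f = 0.20/4 = 0.05; lambda = 0.0025 × 208 = 0.52; power 0.109. Total N for 80%: 788.

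Sensitivity to the true correlation, with effects in SD of the score, N = 52 and analysis of change:

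| rho | SD of change / SD of score | Power, 0.20 SD | Power, 0.52 SD | Difference detectable at 80% |
|---|---|---|---|---|
| 0.3 | 1.18 | 9% | 34% | 0.94 SD |
| 0.5 | 1.00 | 11% | 45% | 0.79 SD |
| 0.7 | 0.77 | 15% | 66% | 0.61 SD |
| 0.8 | 0.63 | 20% | 83% | 0.50 SD |

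**4. If 0.20 and 0.52 are already f.** Power for 0.20 is 0.807, as claimed. For 0.52 it is essentially 100%, but 0.52 then means a difference in change of 4 × 0.52 = 2.08 SD, which is far from medium.

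**5. After drop-out.** 62 × 0.80 = 49.6, so about 50 evaluable patients; power for 0.80 SD is 0.79.

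**The case against.** The strongest reply is that the scale is never named and the source trial is not at hand. The mention of d concerns reporting, not sample-size inputs. If the values, or the authors' conversion of them, were f, then 52 is correct and its power is as stated. This stands, and it limits the point. A reader might infer that 80% power is missed for both effect sizes; the article does not support that as a flat statement.

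Even on the d reading, the source value could be a within-group change or a difference at a single time point. The 45% and 11% require a between-group difference in change at rho = 0.5. With rho = 0.8 the primary-outcome effect of 0.52 SD would reach 83%. The simpler conversion f = d/2, which describes a difference at one time point rather than this interaction, would give 96% for 0.52 (f = 0.26) but only 29% for 0.20 (f = 0.10). So the shortfall for 0.52 depends on assumptions. The shortfall for a d of 0.20 persists at every correlation and under both conversions tried.

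A reader might also infer that a null result would be taken to exclude a small effect. The article does not say so, and it commits to mean differences with 95% confidence intervals, which would show what was not excluded.

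Finally, leaving the correlation to a fuller document is normal for an article and is not held against it here. The point concerns what is stated: labels that do not fit the test used.

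**Conclusion.** The arithmetic behind 52 is sound, but its description is not. Given rho = 0.5, the calculation targets a 0.80 SD between-group difference in change between the two measurements, large by the usual benchmarks. That is so whichever scale the source used.

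What remains open is which error was made. If d values were entered as f, power with 52 patients at rho = 0.5 is about 45% for 0.52 SD and 11% for 0.20 SD (34–83% and 9–20% over rho 0.3 to 0.8). If the values were f throughout, the stated power for 0.20 holds and only the wording is wrong. The article cannot decide between these. The value rho = 0.5 is itself inferred, because of the correlations tried it alone returns 52.

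**What to change.** Keep 62 patients. In the sample-size paragraph:

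- Delete the labels small and medium, or name the scale they refer to, after checking which scale the source trial's values are on.
- State the detectable difference, for example: *Assuming a correlation of 0.5 between measurements and alpha 0.05, the trial has about 80% power for a between-group difference of 0.80 SD in T0–T12 change (0.81 with 52 evaluable participants, 0.79 with the roughly 50 left if 20% of 62 drop out).* The authors should confirm that 0.5 was the value used.
- Do not claim power for a small standardised difference (0.20 SD) in forefoot peak pressure.
- If the source values prove to be d, give the power for 0.52 SD on the primary outcome (about 45% with 52 patients at correlation 0.5, if it is a difference in change).

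The cost is a rewritten paragraph and a less favourable stated sensitivity. No patients, assessments or analyses change.

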## Methods and design

### Trial design

This study is part of a series of two clinical trials: the FOCA trial I (SOPeD intervention) and FOCA trial II (booklet intervention). The FOCA trial I is a superiority, single-blind, randomized controlled trial with two parallel arms where participants will be randomized into one of two groups: the intervention group that will perform foot-related exercises included in the SOPeD; and the control group that will not receive any specific intervention besides the treatment recommended by a health care professional. This trial will have an allocation ratio of 1:1.

People with DM and DPN will be recruited from the Department of Endocrinology of the Hospital das Clínicas of the School of Medicine of the University of São Paulo, Brazil, and will be referred to a physical therapist who will perform the group allocation. The participants will then be referred to another physical therapist who will perform the initial blind assessment. All participants allocated to the intervention group will participate in a protocol of monitored and customized therapeutic exercises for the foot–ankle complex using the SOPeD software three times a week for 12 weeks [40]. After the 12-week period, the intervention group participants will be encouraged to continue exercising until the end of the study following the same schedule set during the intervention period. The participants allocated to the control group will not receive any specific intervention besides the regular treatment recommended by health care professionals (doctors, nurses, and podiatrists). If proven effective, the benefits of the foot-related exercise protocol will be explained and offered to all control participants at the end of the study.

All participants will be assessed at baseline, 12 weeks (end of intervention) and 24 weeks (follow-up). Assessments will record DPN symptoms and severity (primary outcomes) and all other secondary outcomes.

The Consolidated Standards of Reporting Trials (CONSORT) 2010 guidelines will be followed. The study was approved by a research ethics committee (CAAE: 90331718.4.0000.0065) and was registered at ClinicalTrials.gov on 8 July 2019 (study identifier NCT04011267).

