### Participants and recruitment

This study is currently recruiting patients (study start date 1 August 2019) with a medical diagnosis of DM and DPN from the Department of Endocrinology of the Hospital das Clínicas of the School of Medicine of the University of São Paulo through telephone contact. Sixty-two patients with DPN will be recruited. The potential participants will be interviewed by telephone and, upon selection, assessed in the laboratory to confirm all eligibility criteria. This first laboratory assessment will represent the baseline condition (blind assessment).

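### A sample of 62 covers about 16% drop-out, not the stated 20%: keeping 52 patients after 20% loss takes 65, or 66 for equal arms

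*Protocol article*

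**What the plan says.** Under 'Sample size and statistical analyses', the protocol article describes the calculation as follows: "A statistical design of F-test repeated measures and interaction between and within factors with two repeated measures and two study groups", with "a statistical power of 0.80, an alpha of 0.05, and an effect size of 0.20 were used for the sample size calculation". Two effect sizes are listed there: 0.52 for DPN symptoms (primary) and 0.20 for forefoot peak pressure (secondary). The smaller one drives the calculation: "In order to obtain the largest sample size, the smallest effect size (0.20) was used". The outcome is "The resulting sample size was 52 individuals", followed by "A final sample size of 62 patients was then chosen after estimating a drop-out rate of 20" per cent.

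'Participants and recruitment' repeats the total ("Sixty-two patients with DPN will be recruited"), as does the abstract. 'Trial design' fixes equal arms: "This trial will have an allocation ratio of 1:1". The article shows no inflation formula and gives no other reason for 62.

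**The concern.** A drop-out rate is a fraction of those enrolled. An allowance for 20% drop-out should therefore give an enrolment figure that still contains 52 patients after a fifth have been lost, and 62 does not. A reader, or the committee monitoring recruitment, would take the text to mean that losing one patient in five leaves the planned size and 80% power intact. The margin is in fact used up at about one patient in six. All three numbers are printed in the article, so this is an inconsistency in what is stated and not a detail left to a fuller document.

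**Working it through.** **Inputs from the protocol article ('Sample size and statistical analyses').** Two groups, two repeated measures, within-between interaction F-test, alpha 0.05, power 0.80, effect size 0.20, base size 52, drop-out 20%, final size 62. The 1:1 allocation is from 'Trial design'.

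**Assumptions.** The effect size is read as Cohen's *f*. The correlation between repeated measures, ρ, is not stated.

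**Step 1: reproduce 52.** With *m* = 2 measures and 2 groups, the noncentrality is λ = f² × N × m/(1 − ρ), with 1 and N − 2 degrees of freedom. Smallest even N for power 0.80 at f = 0.20:

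| ρ | N |
|---|---|
| 0 | 102 |
| 0.3 | 72 |
| 0.5 | 52 |
| 0.7 | 32 |

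Of these values, only ρ = 0.5 gives 52. There λ = 0.04 × 52 × 2/0.5 = 8.32 and power is 0.807. N = 51 gives 0.7996, just under target, so 52 holds no slack.

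**Step 2: reproduce 62.** 52 × 1.20 = 62.4, which rounds to 62.

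**Step 3: the allowance that 20% requires.** 52/(1 − 0.20) = 65. Equal arms make it 66. Check: 65 × 0.80 = 52.0 and 66 × 0.80 = 52.8.

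**Step 4: what 62 delivers.**
- Patients left at 20% drop-out: 62 × 0.80 = 49.6, so 49 or 50, which is 2 to 3 short of 52.
- Drop-out that still leaves 52: 1 − 52/62 = 16.1%.
- If each patient drops out independently with probability 0.20, the chance of keeping at least 52 is 0.28 with 62 enrolled and 0.57 with 65.

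**Step 5: power for the outcome that set the size** (f = 0.20, ρ = 0.5):

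| Patients | λ | Power |
|---|---|---|
| 49 | 7.84 | 0.783 |
| 50 | 8.00 | 0.791 |
| 52 | 8.32 | 0.807 |

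**Step 6: power for the primary outcome at 50 patients** (same model, ρ = 0.5). If 0.52 is Cohen's *f*, λ = 0.2704 × 50 × 2/0.5 = 54.08 and power is about 1.00. If 0.52 is instead a Cohen's *d*, then f = 0.52/2 = 0.26, λ = 0.0676 × 50 × 2/0.5 = 13.52 and power is 0.95.

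**The case against.** The strongest reply is that nothing turns on this. One or two points of power change no design decision, and the gap is smaller than the uncertainty in an input the article does not give. With ρ = 0.52 in place of 0.5, power is 0.807 at 50 patients and 0.799 at 49, so the shortfall all but disappears. This stands, and it is why the point is minor. It does not make 52, 20% and 62 agree, because that mismatch involves no correlation at all.

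A second reply is that the article plans an intention-to-treat analysis with imputation, so patients who drop out are not simply removed, and it sets no minimum number of evaluable patients. This softens the consequence. However, the sponsor chose to inflate for drop-out, which presupposes that 52 should remain. Imputation does not restore all the information lost, and the planned per-protocol analysis of completers feels attrition directly.

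Three stronger readings are tempting, and the article supports none of them:
- *The primary comparison is underpowered.* The calculation rests on the smaller, secondary-outcome effect size. At the stated 0.52 the primary outcome has ample margin at 49 to 50 patients.
- *The authors are shown to have multiplied by 1.2.* The figure fits that step, but no formula is printed, so it is an inference.
- *Terminations for not using the software and exclusions for new physical therapy reduce the margin further.* These may already be inside the estimated 20%, and the article does not separate them.

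**Conclusion.** The point holds as a minor correction. The stated sample size does not deliver the stated drop-out allowance: 62 covers about 16% loss, and 20% loss leaves 49 to 50 patients where 52 were wanted. That part is plain arithmetic on the article's own figures.

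The power consequence, 78 to 79% against 80%, applies to forefoot peak pressure only. It rests on two assumptions: that 0.20 is Cohen's *f*, and that the correlation between measures is 0.5, a value inferred because it reproduces 52. The ample margin for the primary outcome rests on its stated effect size and the same correlation. The trial's validity is not in question.

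**What to change.** Keep 62 and replace the drop-out sentence with wording such as:

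> A sample of 62 allows for about 16% drop-out with 80% power (f = 0.20, correlation between measures assumed 0.5); at 20% drop-out about 50 remain and power is about 79%.

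The sponsor should confirm the correlation actually entered in the power program and print that value. The cost is one sentence and a slightly less favourable stated allowance, with no added patients. If a true 20% allowance is wanted instead, the enrolment target becomes 65, or 66 for equal arms, which is 3 or 4 more patients, and the figure must then change wherever 62 appears (the abstract, 'Participants and recruitment' and the sample size section).
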